#### Power analysis

The present study is the first to focus exclusively on stimuli-relevant AATP training in addition to TAU in clinical AUD patients, and only one prior study has examined the stimuli-relevant AATP training [26]. This prior study was conducted among subclinical AUD individuals and used a continuous drinking (drinks per day) measure as an evaluation of a stand-alone stimuli-relevant AATP over the web. A small effect at post-treatment (f = 0.17) and close to a medium effect at 3-month follow-up (f = 0.22) was identified [26]. Since our study is targeting a clinical sample with a higher degree of alcohol consumption, it may be easier to detect an effect than in a subclinical AUD sample, however, the AATP training in our study is provided as an add-on to TAU which could dilute the treatment effect compared to the prior study. To be conservative, we only aim to achieve a small additive effect at 3-months follow-up. Since pre- and post-treatment assessments of our intervention are conducted in an inpatient setting rather than over the web, attrition is mainly an issue at the 3-months follow-up assessment. Therefore, we collect only the clinical outcomes that can be measured in a variety of settings (e.g. at treatment, at home, over the phone or through a link on the web). An attrition rate of 30% at 3-month follow-up is assumed.

Based on this, a power analysis (PA) [50, 51] was conducted using G*Power for a repeated-measures ANOVA with α = 0.05; effect size (ES) of f = 0.17; power = 0.80; groups k = 3; time-points measurements = 3; correlations among repeated measures = 0.40; and nonsphericity correction E = 0.60, resulting in a sample size of *n* = 123 participants. To allow for adjustment of the stratification variable, site, an extra 20 patients are required for the final analysis (total *n* = 143). Finally, to account for an attrition rate of 30%, the required sample size is 204 (= 143/(1–0.3)) patients, corresponding to 68 patients in each group.

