## Abstract

**Background:**

The approach-avoidance training program (AATP) has shown preliminary promise as an add-on to standard treatment for alcohol dependence. However, knowledge is lacking as to whether the effectiveness of AATP can be enhanced further when performed in a typical drinking situation. The main aim of this study is to investigate whether approach-avoidance training implemented in a virtual reality bar environment is superior to the classical joystick PC-version of the AATP.

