### Statistical analysis

Descriptive statistics will be calculated to summarize socio-demographic factors, AUD diagnosis and psychiatric comorbidity as well as primary and secondary measures at baseline. Categorical variables will be described using frequencies and percentages. Normally distributed numeric variables will be described using the mean/standard deviation (SD), non-normally distributed numerical variables using the median/interquartile range (IQR).

The main analyses will be conducted with a repeated measures ANOVA, with group as the between-subjects factor and drinks per day the last 30 days at each assessment time-point as the within-subjects factor, to test the effectiveness of the intervention across the assessment points, which would be indicated by a significant Time X Study Group interaction. If there is an overall significant interaction effect between any one time-point and group, we will examine whether the change over time differs between the groups and the time-point using contrasts. Secondary analysis of continuous outcomes will be conducted with repeated measures ANOVA models, with group as the between-subjects factor and other alcohol consumption- (drinking days and drinks per drinking day), craving-, impulsivity- and depressive symptom outcomes as the within-subjects factor. In the case of unbalanced attrition in the randomization groups, mixed models will be applied instead of repeated measures ANOVA. Secondary analysis of dichotomous outcomes (e.g. relapse) will be conducted using mixed model logistic regressions. The analyses will be adjusted for the randomization stratification variable, site, as well as for the outcome values at baseline [48]. Since the study is a randomized controlled trial, other covariates are expected to be balanced across the randomization groups. Missing data will be handled using multiple imputation with changed equation (MICE) methods applying the non-parametric predicted mean matching (PMM) methods [49].

All analyses will be conducted as intention to treat as well as per protocol, and subgroup analyses will be conducted on patients who were successfully treated with conventional or VR-based AATP, defined as completing all six sessions. Further, moderation analyses of approach bias and using anti-craving medication on the treatment effect will be conducted for the primary and secondary outcomes.

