When performing the descriptive and inferential analysis, the researchers will be blinded to the experimental and control groups, and an external statistician will conduct the analysis. The significance level in the models will be set at 5%, and two-sided analyses will be conducted. Effect sizes will be reported in accordance with the statistical modelling. All analyses will be conducted using Stata 16.

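### The power section uses f = 0.17, quoted as an effect at one assessment, unconverted as a 3 × 3 interaction f, so 80% power for a small 3-month effect is not supported; VR versus PC has no stated power

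*Protocol article*

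**What the plan says.** All places are in the protocol article.

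- **Source of the effect size** (Power analysis). An earlier web-based study in a subclinical sample is summarised by assessment: "A small effect at post-treatment (f = 0.17) and close to a medium effect at 3-month follow-up (f = 0.22) was identified".
- **Target** (Power analysis). "To be conservative, we only aim to achieve a small additive effect at 3-months follow-up".
- **Calculation** (Power analysis). G*Power, repeated-measures ANOVA at alpha 0.05, with these main inputs: "effect size (ES) of f = 0.17; power = 0.80; groups k = 3; time-points measurements = 3". The covariance assumptions entered beside them are "correlations among repeated measures = 0.40; and nonsphericity correction E = 0.60". This gives 123 patients. Twenty are added for site adjustment (143), and division by 0.7 for 30% attrition gives 204, or 68 per arm.
- **Main test** (Statistical analysis). A repeated-measures ANOVA of drinks per day, with effectiveness "which would be indicated by a significant Time X Study Group interaction". Contrasts follow if the interaction is significant. "The significance level in the models will be set at 5%, and two-sided analyses will be conducted".
- **Aim** (Abstract, Background). "The main aim of this study is to investigate whether approach-avoidance training implemented in a virtual reality bar environment is superior"; the comparator is the joystick PC version. The Aims section lists this comparison as the second objective. The Power analysis section gives it no effect size and no power.

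**The concern.** In G*Power's default definition, the f for a within-between interaction is the standard deviation of the nine interaction effects (3 groups × 3 times) divided by the common SD. A group difference at one assessment is a different quantity. Turned into an interaction over three assessments, one of which is a pre-randomisation baseline, it shrinks by more than half. The section quotes its f values one assessment at a time, names a one-assessment target, and enters 0.17 with no conversion and no definition of what it measures.

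If the two scales have been mixed, the trial is sized for a much larger effect than the one it names. A null interaction would then be read as evidence against the training, or against VR, when the design had little chance of detecting the named effect. The VR question is more exposed, because the sample size is not tied to it at all.

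**Working it through.** **Inputs from the protocol article:** f = 0.17, k = 3 groups, m = 3 assessments, rho = 0.40, epsilon = 0.60, alpha = 0.05; N = 123, 143 (about 48 per arm) and 204.

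**1. Reproducing 123.** Within-between interaction, default f:

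- λ = f²·N·m·ε/(1 − ρ); df1 = (k − 1)(m − 1)ε = 2.4; df2 = (N − k)(m − 1)ε.
- With f = 0.17 the smallest N is 121 (power 0.803). The next multiple of three is 123: λ = 0.0289 × 123 × 3 × 0.6/0.6 = 10.66, power 0.81.
- At N = 143, λ = 12.40 and power is 0.87. Also 143/0.7 = 204.3.

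Other G*Power variants do not give 123: within factor 98, between factor 204, partial-eta-squared (SPSS-type) f 300. So 0.17 was used as the 3 × 3 interaction f.

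**2. Converting a one-assessment group effect.** If a group effect of size f appears at T3 only, or equally at T2 and T3, the interaction f is f × √(2/9) = 0.471f. If it rises 0, half, full, the factor is 0.408.

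| True group effect | Interaction f | Power at 143 (ε = 0.60) |
|---|---|---|
| 0.17 at T3 only, or equal at T2 and T3 | 0.080 | 27% (36% if ε = 1) |
| 0.17 at T3, half of it at T2 | 0.069 | 21% |
| 0.17 at T2 and 0.22 at T3 | 0.094 | 37% |
| 0.22 at T3 only | 0.104 | 43% |

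For the first row, 80% power needs about 532 evaluable patients.

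**3. Other meanings of f.**

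- *Pre-post (two-assessment) interaction f on the cell-SD scale.* With two assessments the interaction f is half the group f, so the group f is 0.34. The 3 × 3 interaction f is 0.34 × 0.471 = 0.160, and power at 143 is about 82%.
- *Partial-eta-squared-type f.* Power at 143 is about 46% (60% if ε = 1).

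**4. What the interaction test can detect.** At N = 143, 80% power needs an interaction f of about 0.156. For effects at T3 only, or equal at T2 and T3, that is a group f of 0.156/0.471 ≈ 0.33. If both training arms are equal and better than TAU, group f = 0.471d, so d ≈ 0.70 SD.

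**5. VR versus PC.** No difference is stated, so only a detectable difference can be given, as an illustration. Assume 48 per arm, a 3-month comparison, two-sided 5%, and baseline correlation 0.40 (residual SD √(1 − 0.16) = 0.917):

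- Unadjusted: about 2.83 × √(2/48) = 0.58 SD.
- Baseline-adjusted: 0.58 × 0.917 ≈ 0.53 SD.
- Pooled training arms versus TAU (96 versus 48), baseline-adjusted: about 0.46 SD.

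**The case against.** The strongest reply is that nothing has been miscalculated. The chain 123/143/204 reproduces, the powered test is the planned main test, and for an interaction f of 0.17 the claim is true and even understated (87% at 143). That stands: the fault is in what f measures.

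Second, the article does not define the earlier study's f. The words attaching it to an assessment could describe a pre-to-post interaction, which brings power back to about 82%. This also stands, so a reader who concludes that the true power is 27% goes further than the document allows: that figure needs the one-assessment reading, a time pattern and epsilon 0.60. But the pre-post reading does not rescue the text. It implies a group effect of f = 0.34 at 3 months, well above the 0.22 that the section itself calls close to medium.

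Third, patients lost at 3 months still contribute T1 and T2 data, and the analyses adjust for baseline. Even with all 204 patients, the base case reaches only 38%. A baseline-adjusted three-group test at 3 months alone would have about 49% power for f = 0.17 at 143, but that is not the named main test.

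Fourth, a reader might put a power on VR versus PC by doubling f to 0.34 SD, which gives about 44% baseline-adjusted and 38% unadjusted. No section gives such a difference, so that figure cannot be reported as the trial's power. What remains is that the stated sample size has no link to the main aim. A fuller document may cover contrast power, which makes this the weaker part of the point.

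**Conclusion.** The point holds as an unsupported power claim, not as an arithmetic error. The section names a small 3-month effect and does not show 80% power for it.

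- On the natural reading (f = 0.17 between groups at one assessment), power at 143 is about 27%. The range is about 21–37% across time patterns at epsilon 0.60, 36% for the base case if epsilon is 1, and 43% if f is 0.22 at 3 months.
- On the pre-post reading, power is about 82%, for a 3-month effect of f about 0.34.
- Whatever the earlier f measured, for an effect at T3 only or equal at T2 and T3, 80% power at 143 needs a group f of about 0.33. That is about 0.70 SD versus TAU if both training arms are equal. The hypothesised ordering, VR above PC above TAU, would change the SD figure but not the group f.

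The last conclusion does not depend on the cited study. It rests on the protocol's rho and epsilon and on the stated time patterns. Separately, VR versus PC has no stated effect size or power.

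**What to change.** Keep 204 patients, the design and the analysis. In the Power analysis section and the registry entry:

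1. State what f = 0.17 measures in the earlier study, and convert it to the 3 × 3 interaction scale with the assumed time pattern.
2. Replace the claim of 80% power for a small, conservative 3-month effect with what the interaction test can detect at 143 evaluable patients: interaction f of about 0.156, which is a group f of about 0.33 when the effect is at T3 only or equal at T2 and T3.
3. Add detectable 3-month differences at 80% power, labelled as baseline-adjusted contrasts assuming a correlation of 0.40: about 0.53 SD for VR versus PC (0.58 SD unadjusted) and about 0.46 SD for pooled training versus TAU. Note that these are not the power of the interaction test that precedes the contrasts.

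The cost is a text change with no extra patients. The downside is that the stated power becomes less favourable.

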## Ethics

The patients in this study will receive standard treatment at the inpatient clinics and although 66% will receive additional treatment, all patients will be well-treated with evidence-based AUD treatment. Thus, we find no ethical problems with not offering the intervention to the entire sample. However, a critical ethical question is whether using the AATP may encourage patients in the experimental groups to consume alcohol instead of discouraging it. This concern relates to the fact that AAT and AATP involve in vivo exposure to alcohol. However, in European culture, all patients will be exposed to alcohol, both during and after treatment, and they will be unable to avoid this since large-scale alcohol advertisements are on display in the public space, in magazines and on television. Also, alcohol is available, highly visible and easy to buy around the clock in all supermarkets, delicatessens, kiosks and gas stations. Therefore, we consider exposure to alcohol pictures in the experimental groups to be no riskier for the patients than their exposure in everyday life. On the contrary, in the experimental groups, the patients will be trained to avoid alcohol cues and to approach non-alcoholic drinks when exposed in real life. Another ethical question worth considering is whether the VR-based AATP may cause discomfort such as motion sickness (dizziness, nausea, dry eyes etc.). However, patients will not be moving freely around in the VR, which is what usually causes motion sickness. Moreover, the treatment will be performed by healthcare professionals and if any discomfort is experienced, the treatment will be interrupted, and the discomfort alleviated before the end of the training session. Further, we expect the benefits of the VR training to outweigh potential episodes of minor discomfort.

The study protocol has been approved by the research ethics committee in each of the participating countries. In Germany by the local psychological ethical committee at University Medical Center Hamburg-Eppendorf (project-ID: LPEK-0088. In Poland by the Ethical Committee at Pomeranian Medical University in Szczecin (project-ID: KB-0012/162/19). In Denmark by the Regional Scientific Ethical Committees for Southern Denmark (project-ID: S-20190136).

## Discussion

The main aim of this study is to investigate whether stimuli-relevant AATP as an add-on increases the effectiveness of standard treatment and whether stimuli-relevant VR-based AATP is superior compared to the classical joystick PC-version of the AATP.

It is important to emphasize that both the conventional AAT and AATP can be delivered in a stimuli-relevant” and “stimuli-irrelevant” version. In the former version, patients are instructed to focus on the content of the picture (e.g. approach soda, avoid alcohol), whereas in the latter version they are instructed to focus on the format of the picture (e.g. approach horizontal, avoid vertical). Hence, the main difference between the two versions has to do with where the patients’ attention is directed, that is, towards either picture content or an image-irrelevant feature like the picture format. The majority of AAT studies examining AUD and other substance use disorder samples have applied the SI version, even though a recent meta-analysis showed that the stimuli-relevant AAT produces much stronger approach bias measures than the stimuli-irrelevant AAT [52]. Further, alcohol consumption has been found to correlate positively with automatic approach biases in an AUD sample – but only in the stimuli-relevant AAT – suggesting that the stimuli-irrelevant AAT is not a reliable and valid measure of action tendencies in AUD samples [53].

In line with research applying the conventional AAT, only two trials so far have compared the stimuli-relevant and stimuli-irrelevant versions of the AATP in AUD samples [19, 26], whereas other studies have focused exclusively on the stimuli-irrelevant AATP [8, 16, 20]. The first study found the stimuli-relevant AATP to be equivalent to the stimuli-irrelevant version in increasing abstinence rates when delivered as add-on treatment in a clinical AUD sample [19]. The second study demonstrated a superior effect of stimuli-relevant AATP on alcohol consumption compared to the stimuli-irrelevant version in a sub-clinical community sample of AUD individuals [26]. It should be highlighted that none of the AATP studies targeting alcohol approach bias have applied a stimuli-relevant AAT, and this upcoming study is the first to examine whether both stimuli-related and stimuli-irrelevant AAT can be modified by a stimuli-relevant AATP and whether they moderate the effect on clinical outcomes. Studies investigating the effect of AATP on other addictive behavior than AUD have exclusively applied the stimuli-irrelevant version [54–56], which is why it is not possible to draw any inferences from this parallel line of research.

Since the stimuli-relevant AAT and AATP have shown promise in AUD samples, this approach seems particularly suitable for implementation in a VR format, which may be more challenging when directing attention towards image-irrelevant features in natural drinking environments without interfering with its authenticity. To date, VR has primarily been used in attempts to enhance the effectiveness of CET interventions though the induction of cravings. Traditional methods of inducing cravings rely on presenting alcohol in vivo either by placing real alcohol or pictures and videos of alcohol in front of the patient. Although these cues have been shown to induce cravings in some studies [57], and cravings have been shown to predict relapses among AUD patients [58, 59], it has been more difficult to demonstrate a simultaneous decrease in cravings and alcohol consumption in CET trials [11]. Therefore, it has been suggested that, overall, CET interventions may have limited effectiveness because they fail to induce cravings in clinical settings, which is a prerequisite for desensitizing the impulsive system [12, 13]. It has been suggested that integrating alcohol and associated cues in natural drinking environments (e.g. bars, party’s) may be more relevant to induce more cravings than CET, and that VR-based CET may then represent an improvement to CET in that AUD individuals can be taken out of the laboratory or clinical context and placed in an environment with the capacity to induce greater cravings, which in turn might prompt the generalization of treatment to real world activities [12, 60–62].

In sub-clinical and clinical AUD samples, a number of studies have applied VR as an assessment tool to explore alcohol cravings and have found it highly effective in inducing cravings [63–67]. Furthermore, studies examining other drugs of abuse have found that virtual conditions induced more cravings than pictures (e.g. [68–70]. Also, some studies have examined VR-based CET for reducing alcohol-related cravings in AUD samples and found the intervention to be effective in reducing cravings for alcohol [12, 71–73]. The results of assessment and intervention studies are relatively consistent and indicate that if induction of cravings in more alcoholic environments is a major challenge, VR-based CET shows promise for enhancing the treatment of AUD [13].

Cognitive biases and cravings should share a reciprocal relationship, where increases in cravings will make alcohol and associated cues more salient and as these cues become the focus of attention and activate action tendencies they will elicit further increases in subjective craving [74, 75]. Moreover, the association between craving and attentional bias appears to be larger when the strength of craving is relatively high than when it is low at the time of assessment [75], and although this remains to be investigated among substance (ab) users, similar findings have been found between food-craving and approach bias among binge eaters [76].

AATP interventions have to date somehow shown more promise than conventional CET in reducing alcohol consumption but, like with CET, it has been more difficult to prove simultaneous reductions in craving levels and alcohol consumption [8, 19–21]. However, since AAT and AATP also involve in vivo exposure through alcohol pictures, it is plausible that these cues in drinking-related environments may also induce a higher cravings level and cognitive bias, which in turn may improve alcohol consumption measures. In addition to being easier to implement in VR, the stimuli-relevant AATP may have the potential to induce more cravings than the stimuli-irrelevant version because the patients are, like in CET, requested to focus attention on alcohol and associated stimuli [52, 53]. Indeed, it has been suggested that the stimuli-irrelevant AATP may in some cases fail to induce bias because patients totally ignore the content of the picture and only respond to the stimuli-irrelevant content (the format of the picture) due to limits in attention span [77–79]. While assessment tools and interventions targeting attentional biases have exclusively applied stimuli-irrelevant versions (e.g. [14, 15]), in sub-clinical and clinical samples suffering from a wide range of psychiatric disorders, those targeting approach biases can be used in both stimuli-irrelevant and stimuli-relevant versions making them more suitable for VR, where stimuli-relevant versions may be better fitted. However, in this context it is of relevance to notice that a few studies have applied alternate versions of attentional bias modification programs with stimuli-relevant instructions in non-clinical samples to train attentional negative emotional and affective bias. These studies have consistently shown greater or a similar reduction of attentional bias compared to traditional stimuli-irrelevant versions [80–82], which suggests that cognitive bias re-training programs might in general show promise in content relevant versions and be easily implementable in VR formats in the future. Although AATP is already regarded as the most embodied of the cognitive bias re-training programs, the VR format has the potential to make the paradigm even more so. This is because patients are not just requested to actively train action tendencies by reacting with pull vs. push motor responses, but they can navigate in a relatively interactive environment and approach or avoid the alcohol and related stimuli in a wider sense.

In the realm of the available evidence from prior AATP studies it is hypothesized that the two experimental groups will achieve better treatment outcomes (i.e. significantly lower drinking, cravings and impulsivity) compared to the control group, and that the VR-based AATP will achieve better outcomes than conventional AATP at tree month follow-up. The current study will provide important knowledge about the effectiveness of stimuli-relevant AATP and whether its potential effectiveness can be further enhanced by implementing it in a VR bar. If proven effective, future studies should examine the effect of VR-based AATP in the longer term as well as its cost-effectiveness as adjunctive treatment.

Combining psychological treatments that address AUD-related cognitive dysfunctions in the reflective and impulsive systems might better prepare patients for their inevitable confrontation with alcohol in their natural environment and increase the probability of preventing relapses in the longer term. The stimuli-relevant VR-based AATP can, like the stimuli-relevant conventional AATP, be implemented easily and cheaply as add-on treatment or continued care to enhance the effectiveness of current evidence-based treatment.

